#### Outcomes {12}

##### Primary outcomes

The following primary outcomes are shown in Table 1:
Child cognitive development at 24 months of age, assessed using the Bayley Scales of Infant and Toddler Development III (BSID-III) cognitive subscale.Maternal perinatal depression at 12 months postnatal assessed using the Edinburgh Postnatal Depression Scale (EPDS).

**Table 1 Tab1:** Primary outcomes

Domain	Measure	Metric	Method of aggregation	Timepoint
Child cognitive development at 24 months of age	Bayley Scales of Infant and Toddler Development III (BSID-III) cognitive subscale (Composite Score)	Mean difference	Mean and SD	24 months postnatal
Maternal depression	Edinburgh Postnatal Depression Scale (EPDS), total score	Mean difference	Mean and SD	12 months postnatal

##### Secondary outcomes

The 10 secondary outcomes and the associated measures are summarised in Table 2 and Table 3.

**Table 2 Tab2:** Secondary outcomes

	Domain	Measure	Metric	Method of aggregation	Timepoint
1	Maternal depression	Edinburgh Postnatal Depression Scale (EPDS), total score	Mean difference	Mean and SD	End of pregnancy; 24 months postnatal
2	Maternal anxiety	Generalized Anxiety Disorder 7-item (GAD-7) scale, total score	Mean difference	Mean and SD	End of pregnancy, 24 months postnatal
3	Maternal antiretroviral treatment adherence	Viral Suppression (Yes/No)	Risk ratio	Frequency and percentage	End of pregnancy; 12 weeks, 12 months, 24 months postnatal
4	Exclusive breastfeeding	Exclusive breastfeeding at 6 months (Yes/No)	Risk ratio	Frequency and percentage	6 months postnatal
5	Adherence to infant immunisation schedule over the 24-month postnatal period	No. of immunisations recorded	Mean difference	Mean and SD	12 weeks, 12 months, 24 months postnatal
6	Infant diarrhoea	Any maternal report of diarrhoea over the previous 14 days.	Risk ratio	Frequency and percentage	12 weeks, 6 months, 12 months, 24 months postnatal
7	Cognitive and emotional stimulation within the home environment	Early Childhood Development section of Multiple Indicator Cluster Surveys (MICS6) Questionnaire for cognitive and emotional stimulation for children under five, total score	Mean difference	Mean and SD	12 months, 24 months postnatal
8	Infant behaviour	Parenting Stress Index, Short Form (PSI/SF: parent-child dysfunctional interaction subscale and difficult child subscale, total score	Mean difference	Mean and SD	12 months postnatal
		Externalising subscale of Child Behaviour Checklist (CBCL), total score	Mean difference	Mean and SD	24 months postnatal
9	Child language development	Language subscale of the Bayley Scales of Infant and Toddler Development III (BSID-III), Composite score	Mean difference	Mean and SD	24 months postnatal
10	Child growth (infant height and weight at 24 months)	Road to Health Book, study Weight and height measurements	Mean difference	Mean and SD	24 months postnatal

**Table 3 Tab3:** Mediators, including measures and timepoints

Mediators	Measure	
Family, relationship support and conflict	Relationship conflict questions adapted from the Romantic Partner Conflict Scale [59]. Support questions used from social support measure previously validated in South Africa [60].	Baseline, end of pregnancy, 12 weeks, 12 and 24 months
Rumination	Brief Rumination Response Scale [61]	Baseline, end of pregnancy, 12 weeks, 12 and 24 months
Maternal recognition of infant faces and sounds	Stimuli task	Baseline, 12 months

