#### Secondary objectives:

To identify if the combined intervention compared to the ESoC:
Improves maternal depression at end of pregnancy^1^ and 24 months postnatal.Improves maternal anxiety at the end of pregnancy and 24 months postnatal.Increases maternal adherence to Antiretroviral Treatment (measured as viral load (VL) and viral suppression post-initiation of treatment) over the trial period.Increases rates of exclusive breastfeeding to six months postnatal.Improves adherence to infant immunisation schedule over the 24-month postnatal period.Reduces episodes of diarrhoea over the postnatal period^2^.Improve the quality of infants’ cognitive and emotional stimulation within the home environment at 12 and 24 months.Reduces child behavioural difficulties at 12 and 24 months postnatal.Improves child language development at 24 months postnatal.Improves child growth (infant height and weight) at 24 months postnatal.

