### Additional consent provisions for collection and use of participant data and biological specimens {26b}

No biological specimens will be collected in the trial.

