**Secondary outcomes**										
EPDS	X			X			X			X
GAD-7		X		X					X	X
Maternal Antiretroviral treatment adherence		X		X			X		X	X
Exclusive Breastfeeding								X		
Infant immunisations							X		X	X
Infant diarrhoea							X	X	X	X
Cognitive and emotional stimulation (MICS)									X	X
Infant Behaviour (PSI/SF and Externalising subscale CBC)*									X	X
BSID-III language										X
Child Growth (weight and height)							X		X	X

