##### Recruitment strategy

The recruitment process is led by recruiters from the trial team with support from DoH antenatal nurses and clinic clerks.

Recruitment into the trial occurs through a four-stage process:
Identification of potential participants—Clinic records are reviewed by antenatal nurses and clinic clerks at antenatal clinics to identify HIV-positive, pregnant women (gestational age 23–33 weeks) over the age of 16 years. The nurses and clerks reassure the potential participants that their clinical care will not be compromised by participation.Referral to recruiter—If the identified potential participants consent, they are referred to a trial recruiter who explains the trial procedures and screens for additional eligibility criteria.Depression screen—Administration of the EPDS if the potential participant meets all other eligibility criteria.Consent processes—Written consent and scheduling of baseline assessment at home for participants who fulfil all inclusion criteria, including an EPDS ≥ 9.

The baseline assessment is conducted at the home at which point the GPS location is verified. The participant is randomised (based on their geospatial cluster) following the baseline assessment.

Only participants who were diagnosed with HIV at least 2 weeks previously and have been initiated on ART are recruited.

If during the screening or recruitment process a participant indicates thoughts of self-harm on the self-harm item of the EPDS, this initiates a risk management response and immediate notification is then made to the Trial Coordinator and Trial Psychologist. The Trial Psychologist then makes a psychological assessment in order to establish whether there is active suicidal intent or behaviours. It these are present, the psychologist undertakes initial management including telephonic follow-up at 24 h, 48 h and 72 h, and referral to the DoH Psychologist at the local hospital as appropriate. Following this management, if the potential participant is no longer at risk for self-harm, and still meets recruitment criteria, then they will be offered participation in the study.

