### Plans for collection, laboratory evaluation and storage of biological specimens for genetic or molecular analysis in this trial/future use {33}

Not applicable, no biological samples are collected.

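### Baseline viral suppression should be a prespecified covariate for the viral-suppression risk ratios, not one that enters only if the arms happen to differ

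*Protocol article*

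**What the plan says.** The secondary objective on antiretroviral treatment (ART) is that the intervention increases adherence, "measured as viral load (VL) and viral suppression post-initiation of treatment) over the trial period". Table 2, row 3, makes this a binary outcome, viral suppression, reported as a risk ratio at "End of pregnancy; 12 weeks, 12 months, 24 months postnatal".

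Table 4 (Participant timeline {13}) has a row "Maternal Antiretroviral treatment adherence". It is marked at baseline as well as at the four outcome timepoints.

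Section {20a} gives binary outcomes a mixed-effects binomial or Poisson model and does not mention the baseline value of the outcome. It brings in baseline by name only for the EPDS and the GAD-7, through their repeated-measures models. For everything else there is a general rule: the adjusted model, which carries the primary inference, takes in baseline differences between the arms that are judged important, and differences between women followed to 24 months and women lost.

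Two further statements bear on what baseline viral status means here. On entry: "Only participants who were diagnosed with HIV at least 2 weeks previously and have been initiated on ART are recruited". On sampling: "No biological specimens will be collected in the trial", repeated under {33} as "Not applicable, no biological samples are collected".

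**The concern.** The trial plans to hold a baseline value of the adherence outcome, and a woman's viral status at entry is likely to predict her later status strongly. Yet whether that value is used depends on how the arms turn out. If they look balanced, the covariate may be left out and its precision lost. If they look moderately unbalanced, someone must decide, after seeing the data, whether the difference is important. The article gives no criterion for that decision.

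Entry also mixes women long established on ART with women who may have started about two weeks earlier. This adds variation in viral status that has nothing to do with the counselling, most of all at end of pregnancy.

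At stake are the precision of one secondary result and freedom from a choice of covariates that can be made after the fact. The validity of either primary outcome is not in question.

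**Working it through.** **Is baseline in the model?** The article states no rate, effect size or power for viral suppression, so there is no figure of its own to reproduce. Comparing the sections:

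| Outcome | Baseline marked in Table 4 | Baseline named in {20a} |
|---|---|---|
| EPDS | at screening and enrolment | yes, repeated-measures model |
| GAD-7 | yes | yes, repeated-measures model |
| ART adherence (viral suppression) | yes | no; general rule only |

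**How large can a chance imbalance be?** From the Sample size section: 264 women per arm, 48–60 clusters (24–30 per arm) and an ICC of 0.05. That ICC was set for the BSID-III and is borrowed here. Baseline suppression p is assumed to be 60–90%.

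- Women per cluster m = 264/k; design effect DE = 1 + (m − 1) × 0.05. For k = 24, 28 and 30 this gives 1.50, 1.42 and 1.39.
- SE of the baseline difference between arms = √[2p(1 − p)/264 × DE].
- With p = 0.8 and k = 28: √[2 × 0.16/264 × 1.421] = 0.0415, so the 95% range is ±1.96 × 0.0415 = ±8.1 percentage points.
- Over all combinations, the range runs from ±6.0 points (p = 0.9, k = 30) to ±10.2 points (p = 0.6, k = 24).

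If importance were judged by a 5% significance test (an assumption), every difference inside these ranges, about 95% of chance imbalances, would be left unadjusted.

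**What would that do to the outcome?** Assume later suppression of a = 93% in women suppressed at baseline, and b = 40–60% in the others. A baseline imbalance d moves the crude outcome difference by d × (a − b). With k = 28, d = 8.1 points (p = 0.8) and a − b = 0.33 give 2.7 points; d = 10.0 points (p = 0.6) and a − b = 0.53 give 5.3 points.

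**How much variance does baseline explain?** R² = p(1 − p)(a − b)²/[P(1 − P)], where P = pa + (1 − p)b.

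- p = 0.8, b = 0.6: P = 0.864; R² = 0.16 × 0.1089/0.1175 = 0.15.
- p = 0.7, b = 0.4: P = 0.771; R² = 0.21 × 0.2809/0.1766 = 0.33.

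For p between 0.5 and 0.8, R² stays within about 0.15–0.33. On a linear scale this is worth a sample larger by 1/(1 − R²), roughly 1.2 to 1.5 times. It is only a guide, because R² does not translate directly into precision for a mixed-effects risk ratio.

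**Time on ART.** Take a woman who started ART two weeks before enrolment. Enrolled at 33 weeks, she has 36 − 33 + 2 = 5 weeks of ART at 36 weeks of gestation, 7 at 38 and 9 at 40. Enrolled at 23 weeks, she has 15, 17 and 19. The spread matters at end of pregnancy and much less at 12 or 24 months.

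**The case against.** **Baseline is not excluded.** The general rule in {20a} could bring viral status in, and the article names hardly any covariates, a detail often left to the analysis plan. This stands as far as it goes: a reader might infer that the baseline value is discarded, and the text does not say so. But the article does fix a rule for choosing covariates, and that rule rests on observed differences. The rule can be criticised as written.

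**Randomisation deals with time on ART.** It balances ART duration in expectation, and an unadjusted interval already allows for chance imbalance. This stands. The case for adjustment is precision and a choice made in advance, not removal of a systematic bias.

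**Results drawn before allocation.** Because the trial takes no specimens, a reader might infer that viral loads come from routine care and that an old result could be scored as the end-of-pregnancy outcome. The article states no such rule. Table 4 places end of pregnancy in the post-allocation period, and the objective refers to suppression after treatment starts. The source, sampling window and suppression threshold may be in the full protocol or analysis plan, and collecting no specimens is compatible with using routine results. This is a point to confirm, not an error.

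**Baseline may be patchy.** That the baseline entry in Table 4 is viral status is inferred from Table 2, which measures adherence by viral suppression. Women who have just started ART may have no usable result. This stands and is part of the cost.

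**Conclusion.** The point holds as a low-cost improvement to one secondary outcome. The adherence outcome is marked at baseline, but for viral suppression {20a} lets it into the model only through a rule that depends on observed differences. Fixing the covariate in advance is better.

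The sizes are illustrative: chance baseline differences within about ±6 to ±10 percentage points, and 15–33% of outcome variance explained by baseline. They rest on assumed suppression rates and a borrowed ICC, not on figures for this outcome in the article. That baseline status predicts later suppression strongly is itself an expectation. The benefit is likely to be greatest at end of pregnancy, when newly initiated and established women differ most.

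The documents do not support the stronger conclusions that baseline viral status goes unused, that time on ART biases the comparison of arms, or that results drawn before allocation are counted as outcomes. Neither primary outcome is affected.

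**What to change.** In {20a}, add that the viral-suppression risk ratios at all four timepoints are adjusted for baseline viral suppression, whatever the observed imbalance. Where the ART start date is recorded, also adjust for newly initiated versus established ART at enrolment, with the cut-off defined in advance.

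State how a missing baseline result is handled, by a missing-baseline category or by imputation. The multiple imputation in {20c} covers only the primary outcomes, so this needs its own sentence. Missing results are most likely in women who have just started ART.

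Separately, confirm that the full protocol or analysis plan gives the source of viral loads and the sampling window for each timepoint. If it does, nothing more is needed on that point.

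The cost is a few lines of analysis wording, with no new visit, sample or treatment change. The one drawback is the extra handling of missing baseline results.

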### Statistical methods

#### Statistical methods for primary and secondary outcomes {20a}

The primary inference will be based on the BSID-III cognitive score at 24 months and the EPDS at 12 months. For the primary outcomes and other continuous outcomes, the mean (SD) will be presented by the allocation group, and the mean difference (plus 95% confidence interval) will be estimated using mixed-effects linear regression. For binary outcomes, the number and percentage with the outcome will be presented by the allocation group, and the risk ratio (plus 95% confidence interval) will be estimated using a mixed-effect binomial or Poisson regression model.

The unit of randomisation is a geospatial cluster as outcomes are collected at the individual level, hence the unit of analysis is the mother and the infant. There is also an additional level of clustering by the counsellor delivering the intervention. The lack of independence amongst individuals in the same cluster and standard methods of analysis will underestimate the standard error of the treatment difference yielding *p* values that are too small. To account for the correlation of outcomes within clusters, the geospatial cluster and counsellor identifier will be fitted as random effects, with counsellor nested within the geospatial cluster. The intra-class correlation coefficients for geospatial cluster and counsellor will be estimated.

For the EPDS and the GAD-7, a repeated measures model will be fitted, including the baseline, end of pregnancy and 12-month and 24-month scores. For the cognitive and emotional stimulation at home outcomes, a repeated measures model will be fitted including the 12- and 24-month scores. Mixed-effects models with maximum-likelihood estimation allow participants with incomplete repeated measures data to be included in the model, contributing to the estimation of model parameters. The mean scores with 95% confidence intervals will be plotted over time by the allocation group.

In addition to adjusting for important baseline differences between randomised groups, any differences between participants followed up to 24 months and those lost to follow-up will be adjusted for in the final models. Both unadjusted and adjusted models will be fitted, but the primary inference will be based on the adjusted model which provides unbiased estimates if the outcome data is missing at random (i.e. only dependent on observed characteristics).

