## Trial status

The trial started recruitment on 04/04/2018. Recruitment was suspended on 16/03/2020 due to the COVID-19 pandemic and was resumed briefly for 6 weeks in November and December 2020 but had to be paused in December 2020 due to further COVID-19 restrictions. Recruitment resumed again in March 2021 and was the closed on 13th of July 2021. The trial is currently operating on protocol version V1.05 (26th of May 2021 ).

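### The raw count of recorded immunisations is an insensitive, age-dependent proxy for adherence to the infant immunisation schedule (secondary outcome, minor)

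*Protocol article*

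**What the plan says.** The protocol article's secondary objectives include this one: "Improves adherence to infant immunisation schedule over the 24-month postnatal period". Table 2, row 5, carries the same construct as its domain, "Adherence to infant immunisation schedule over the 24-month postnatal period". It fixes the measure as "No. of immunisations recorded", summarised by mean and SD, with the metric "Mean difference", at "12 weeks, 12 months, 24 months postnatal". In Table 4 the row "Infant immunisations" is marked at the same three assessments.

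Under Statistical methods {20a}, for continuous outcomes, "the mean difference (plus 95% confidence interval) will be estimated using mixed-effects linear regression". The adjustments named there are for important baseline differences and for differences between participants followed up and those lost. Age at the visit is not among them. The repeated-measures models are reserved for the EPDS, the GAD-7 and home stimulation, so the immunisation count is not covered by one.

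**The concern.** A schedule says which doses are due by which age, so adherence to it has two parts: whether the due doses were given, and whether they were given on time. The measure in row 5 has no doses-due denominator and no timing criterion. Two consequences follow.

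- **Catch-up is invisible between visits.** A child who had every dose late but caught up before the visit scores the same as a child vaccinated on time.
- **The count depends on age.** Two equally adherent children, one seen just before a due date and one just after, receive different scores.

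Other rows of Table 2 do judge behaviour against a standard: row 3 (antiretroviral adherence) uses viral suppression yes/no, and row 4 uses exclusive breastfeeding at 6 months yes/no. At stake is whether a real gain in timeliness would show in the result, and whether a null result could be read as no effect on adherence.

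**Working it through.** The article states no power, rate or coverage for this outcome, so there is no figure of the plan's own to reproduce. The check compares the stated construct with the fixed measure and then illustrates the gap.

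**Assumptions (none from the documents; for arithmetic only, not a proposed vaccination schedule).** Sixteen doses: 2 at birth, then 4, 2, 4, 1, 1, 1 and 1 due at 6, 10, 14, 26, 39, 52 and 78 weeks. Every child eventually receives all doses. Each child has one exponential delay with mean *m* weeks, applied to all doses after birth. On time means within 4 weeks of the due age. Visits fall at exactly 12, 52 and 104 weeks.

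**Formulas.**

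- Share on time = [2 + 14 × (1 − exp(−4/*m*))] / 16.
- Mean count at visit age *v* = 2 + Σ (doses due at age *d* < *v*) × (1 − exp(−(*v* − *d*)/*m*)).

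**Numbers put in, for *m* = 8.**

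- On time: [2 + 14 × 0.3935] / 16 = 7.509/16 = 0.469.
- 12-week count: 2 + 4 × (1 − exp(−6/8)) + 2 × (1 − exp(−2/8)) = 2 + 2.111 + 0.442 = 4.55.

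A simulation of 200,000 children per setting gave:

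| Mean delay (weeks) | Doses on time | Count at 12 weeks | Count at 12 months | Count at 24 months |
|---|---|---|---|---|
| 1 | 98% | 7.72 | 14.00 | 16.00 |
| 4 | 68% | 5.90 | 13.96 | 16.00 |
| 8 | 47% | 4.55 | 13.71 | 15.96 |

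The assumed 52-week dose falls on the 12-month visit day, so any delay leaves it unrecorded there. The highest count in that column is therefore 14.

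**Sensitivity to delay.** From a mean delay of 1 week to 8 weeks, the count loses 14.00 − 13.71 = 0.29 doses at 12 months and 16.00 − 15.96 = 0.04 at 24 months. At 12 weeks it loses 7.72 − 4.55 = 3.17 of the 8 doses due. The early visit registers delay; the two later ones barely do.

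**Sensitivity to age.** A child vaccinated exactly on schedule scores 8 if seen at 12 weeks and 12 if seen at 14 weeks; 14 at 48 weeks and 15 at 52 weeks; and 16 at both 100 and 110 weeks. The effect is present near a due date and absent around 24 months.

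**What a doses-due denominator does.** The same child scores 8/8 = 1 and 12/12 = 1 at 12 and 14 weeks, so the age effect goes. Late catch-up remains hidden: with *m* = 8 the 24-month ratio is 15.96/16 = 0.9975. Only dose dates show timeliness.

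**The case against.** The strongest reply is that the count is taken three times, at the same nominal ages in both arms. A dose never given lowers it, and so does a delay that runs past a visit. The 12-week column above shows that it can respond strongly. This stands, and the reader should not infer that the count fails to measure adherence at all.

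A second reply is that visit windows and adjustment for age are commonly left to the full protocol or the analysis plan. That also stands, and their absence from the article is not criticised here. But measure, metric, aggregation and timepoints are all fixed in Table 2, and an analysis plan that followed the table would compare raw counts.

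Three stronger readings are tempting and unsupported:

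- **A biased arm comparison.** The intervention arm has more contact (ten home sessions and a booster, against four calls), so one might infer that the arms are seen at different ages. The documents show no such difference. The assessment schedule is the same, assessors are blinded, and tracing methods are not described as differing by arm. Without a difference in visit age, the age effect is noise.
- **Disturbed visit timing in the pandemic.** The Trial status section says: "Recruitment was suspended on 16/03/2020 due to the COVID-19 pandemic". That concerns recruitment and says nothing about the timing of follow-up visits.
- **Most children at the maximum count.** The article gives no coverage figures, so this cannot be asserted.

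**Conclusion.** The point holds in a limited form. Row 5 names adherence to a schedule and measures cumulative uptake. The measure detects missed doses and delays that cross a visit, ignores delay made good before the next visit, and near a due date carries variation from the child's exact age.

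How much this matters cannot be computed from the documents. In the illustration, a drop of about 51 percentage points in on-time doses (98% to 47%) moves the mean count by 0.29 doses at 12 months and 0.04 at 24 months, but by 3.17 at 12 weeks. These figures rest wholly on the assumed schedule, the assumed delay distribution and eventual full vaccination.

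Severity is minor. This is one of ten secondary outcomes, and neither the sample size nor the inference on the two primary outcomes depends on it.

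**What to change.** In Table 2, row 5:

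1. Score the outcome against the schedule, as doses received out of doses due at the child's actual age on the visit day. Analysing the count with doses due, or age at the visit, in the model serves the same purpose. Keep the raw count as description.
2. Where dose dates are available from the vaccination record, add the proportion of due doses given on time within a window stated in advance, so that late catch-up is not credited as adherence.
3. If dates are not available, label the outcome as the number of immunisations received and draw no conclusion about timeliness.

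No new visit is needed. The cost is some derivation work: doses due must be computed from each child's age at the visit against a named schedule. The main uncertainty is step 2. The article does not say that dose dates were captured and recruitment has closed, so step 3 may be the realistic choice.
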